**Secondary**

1. All-cause mortality
2. Annual rate of moderate or severe COPD exacerbations
3. Annual rate of moderate COPD exacerbations
4. Annual rate of severe COPD exacerbations
5. First moderate COPD exacerbation
6. First severe COPD exacerbation
7. Annual rate of hospitalizations for pneumonia
   1. Follow up and censoring

**Primary effectiveness and safety outcomes**: Follow up starts 1 day after the cohort entry date and continues until any of the following occurs:

(1) discontinuation of index therapy (with a 60-day grace period between fills and a 60-day exposure risk window)

(2) switch from exposure to referent or vice-versa

(3) initiation of a different inhaler regimen (ICS, LABA, ICS-LABA, LAMA-LABA, ICS-LABA-LABA)

(4) death

(5) the end of insurance coverage

(6) the end of data

(7) 365 days

1. **Statistical analysis**: For our primary balancing methodology, we will perform inverse probability of treatment weighting (IPTW) with stabilized weights using propensity scores estimated from an over-identified covariate balancing propensity score (CBPS) model. We specified a logistic regression model for the CBPS estimation procedure, including the variables in Table 1 as predictors of exposure.

CBPS augments standard GLM propensity score estimation by imposing additional balance constraints, optimizing the likelihood function while iteratively “nudging” coefficient estimates toward a model that maximizes covariate balance between groups.^6,7^ This method has been shown to offer increased robustness to propensity score model misspecification, improved covariate balance in observational data, and reduced bias in estimating treatment effects compared to logistic regression, while still maintaining its ease of interpretability.^6,8^ IPTW is a standard method for estimating the average treatment effect (ATE), and the use of stabilized weights can offer increased precision.^9–11^ Furthermore, we found that CBPS-IPTW performed the best in our particular dataset in terms of achieving strong balance while avoiding extreme weights that could bias our estimates.^12^ This balance assessment is summarized in Table 2, which compares several methods on a set of important balance metrics.^7,13,14^ While entropy weighting outperformed in several important balance metrics, it made less efficient use of the data with a lower effective sample size (ESS) in the exposure group and also had extremely large weights that could bias our estimates. Several other metrics were also computed for both the main effect and higher order terms, such as the maximum standardized mean difference (SMD), the maximum Kolmogorov-Smirnov (KS) for higher order terms, the number of variance ratios greater than 0.5 and less than 2, the number of SMDs for higher order terms that exceeded 0.1, and finally, the ESS, weight ratio, and coefficient of variability (CV) for the referent group. However, these metrics were comparable between all the methods, and were therefore excluded from Table 2.

**
[figure not shown]
**

To estimate the relative average treatment effect (ATE) on our time-to-event outcomes (including the primary effectiveness and safety outcomes, as well as our secondary outcomes of moderate COPD exacerbation and severe COPD exacerbation), we will estimate marginal hazard ratios (HRs) using Cox proportional hazards models of the respective outcome with the treatment as the sole predictor and incorporating balancing weights from CBPS-IPTW.^10,12^ The corresponding 95% confidence intervals will be estimated using cluster-robust standard errors (SEs).^12^ To estimate the ATE on annual rates of recurrent time-to-event outcomes (our secondary outcomes of annual rates of COPD exacerbations and pneumonia hospitalizations), we will use a Prentice, Williams, and Peterson Total Time Model in the weighted cohort, with a 14-day washout period after each exacerbation. This modified version of the Cox model does not assume constant baseline risk or independence between recurrent outcomes for a given individual, which is consistent with what we know about the increasing risk of subsequent COPD exacerbations.^15–19^ We will report both unadjusted and adjusted results for primary and secondary outcomes. In addition to hazard ratios, we will present the number of outcomes, mean duration of follow up, and reasons for censoring stratified by exposure. We will also produce adjusted cumulative incidence curves for both primary outcomes.^20,21^

1. **Subgroup analyses**

|  | **Subgroup*** | **Why?** | **Strengths** | **Weaknesses** |
| --- | --- | --- | --- | --- |
| **1** | 1 or more baseline moderate or severe COPD exacerbations | ICS-based regimens are thought to be especially valuable for those who frequently exacerbate. This subgroup analysis seeks to examine the comparative effectiveness of Advair Diskus and HFA in this population where ICS-based regimens are thought to be particularly beneficial. | Addresses comparative effectiveness and safety in high-risk patients | None |
| **2** | 1 or more baseline COPD hospitalizations | ICS-based regimens are thought to be especially valuable for those who frequently exacerbate. This subgroup analysis seeks to examine the comparative effectiveness of Advair Diskus and HFA in this population where ICS-based regimens are thought to be particularly beneficial. | Addresses comparative effectiveness and safety in high-risk patients | Low power |
| **3** | Prior diagnosis of asthma | GOLD guidelines recommend ICS-containing regimens for those with a prior diagnosis of asthma. This subgroup analysis seeks to examine the comparative effectiveness of Advair Diskus and HFA in this population where ICS-based regimens are thought to be particularly beneficial. | Addresses comparative effectiveness and safety in lower risk subgroup | None |
| **4** | Excluding patients with recent asthma diagnosis codes (in prior 3 years). | GOLD guidelines recommend ICS-containing regimens for those with a prior diagnosis of asthma. This subgroup analysis seeks to examine the comparative effectiveness of Advair Diskus and HFA in this population where ICS-based regimens are thought to be particularly beneficial. | Addresses comparative effectiveness and safety in lower risk subgroup | Low power |
| **6** | Spirometry before cohort entry | Maintenance inhalers are more likely to be effective for patients who have a proven diagnosis of COPD (as measured by spirometry). We want to examine whether, among patients with spirometry (i.e. patients most likely to benefit from inhaler therapy), there is any difference between Advair Diskus and HFA. | Addresses comparative effectiveness and safety in population enriched for COPD (closer to RCT population) | We do not know the actual measurements from the spirometry. |
| **7** | Index-prescription from a pulmonologist | Pulmonologists may be more likely to assign guideline-recommended therapy compared to other practitioners. We will examine whether Advair HFA has similar effectiveness to Advair Diskus among patients whose index prescription is from a pulmonologist. | Addresses generic quality in population enriched for patients who should be receiving guideline-concordant care. | Low power. |
| 8 | Cohort entry between 2007-2018 | This is the primary time during which Advair Diskus and Advair HFA were on the market without generic competition, limiting confounding from competing devices that patients might be alternatively prescribed. | Limits confounding from competing inhalers, providing a more direct comparison of Advair Diskus vs. HFA. | None. |
| 9 | Cohort entry between 2019-2023 | This study period includes both the approval of the first generic fluticasone-salmeterol (Wixela Inhub) in 2019, as well as the COVID-19 pandemic (starting in 2020). These events could potentially confound our estimate of the ATE due to changes in treatment selection, as well as respiratory outcomes, care, and hospitalizations due to COVID-19. | Allows us to observe how the ATE changes relative to our overall estimate during a period that includes COVID-19 and a major generic approval, which could flag potential confounding in the overall cohort. | Changes in ATE are likely due to unobserved confounders rather than comparative intrinsic effectiveness/safety between the Advair devices. |
| 10 | Gender (Male/Female) | COPD severity, incidence, and care has been observed to vary across various demographic dimensions; large observational studies such as this allow us to observe patients who are often excluded from clinical trials.^22–26^ | Allows us to observe potential heterogenous treatment effects between different demographic groups that often have inadequate representation in RCTs. | None. |
| 11 | Race (White/Black/  Hispanic/Asian) |  |  |  |
| 12 | Age (less than 65 vs. 65 and older) |  |  |  |

*Each subgroup analysis will be performed with patients who meet the definition (for example, at least 1 baseline COPD exacerbation) and those who do not meet the definition (for example, no baseline COPD exacerbations).

1. **Sensitivity analyses**

|  | **Sensitivity** | **Why?** | **Strengths** | **Weaknesses** |
| --- | --- | --- | --- | --- |
| **1** | Alter the grace period for continuous use (30 days, 90 days). | This allows us to assess whether estimates differ when the exposure definition changes. | Using a shorter grace period (30 days) will provide more specificity with respect to the exposure while the longer grace period (90 days) will better reflect real-world practice. | 30-day grace period will exclude people who are truly exposed, while 90-day grace period will include people are not truly exposed |
| **2** | ITT over one year of follow-up | We will assess whether there are differences between Advair Diskus and Advair HFA in a truly real-world setting in which patients frequently discontinue therapy. | This analysis will allow us to avoid informative censoring. | Much of the included person-time will be unexposed person-time. |
| **4** | Exclude the first 30 and 60 days after cohort entry. | Patients may receive ICS-LABAs when their symptoms are bad (but before a true moderate or severe COPD exacerbation). We will assess whether any differences between Advair Diskus and Advair HFA exist when we exclude these early exacerbations. | This allows us to focus on the long-term effectiveness of these maintenance therapies. | Follow-up time will be low because patients discontinue their inhalers so frequently. We may not have sufficient power to detect small treatment effects in this analysis. |
| **5** | Alter the definition of a moderate exacerbation: (a) require an office or ED visit before the prednisone fill; (b) require both prednisone (5-14 days) and a respiratory antibiotic; (c) count either a prednisone script (5-14 days) or a respiratory antibiotic script | This will allow us to assess the robustness of the results to variations of the outcome definition. | Each of these outcome definitions has been employed elsewhere in the literature. | (a) We will exclude many patients who have moderate COPD exacerbations but do not come into clinic. (b) We will exclude many patients who are having moderate exacerbations (antibiotics + steroids are only recommended for patients meeting specific criteria such as purulent sputum); (c) We will include patients who receive antibiotics for reasons having nothing to do with COPD exacerbations |
| **6** | Alter the definition of a severe exacerbation: allow for a COPD diagnosis in any position for the hospitalization | This will allow us to assess the robustness of the results to variations of the outcome definition. | The outcome definition in the primary effectiveness analysis may exclude patients who are having a COPD exacerbation but are admitted for a different primary reason (e.g. MI). | This is a less specific definition than the one we employed since many patients will have a code for COPD during a hospitalization even though they are not having an exacerbation. |
| **7** | Alter the definition of pneumonia hospitalization: require that the pneumonia diagnosis occur in the primary position for the hospitalization | This will allow us to assess the robustness of the results to variations of outcome definition. | The outcome definition in the primary safety analysis may capture patients with mild pneumonias. This will capture only the more severe pneumonias. | Pneumonias are a known side-effect of ICS-LABAs, and this sensitivity analysis will miss many clinically important pneumonias. |
| **8** | Logistic regression propensity score estimation | Given that we are using an augmented version of logistic regression to estimate propensity scores for our primary analysis, it will be informative to see how our estimates differ when we use standard logistic regression. | Allows comparison of our chosen propensity score estimation method with a standard method. | Might not be able to capture more complex relationships between the covariates (interactions, polynomial terms, etc.). |
| **9** | Entropy weighting | Balancing our cohort with a method that does not rely on propensity scores will allow us to gauge the robustness of our estimates to potential bias resulting from propensity score misspecification. | Balances covariates without the need to specify a propensity score, allowing us to gauge the robustness of our primary estimates. | Entropy weighted estimation can estimate a target estimand that deviates from the ATE in settings with high or low exposure prevalence.^27^ |
| **10** | High-dimensional propensity score matching | HdPS adjusts for hundreds of empirically defined covariates. | Rigorous, alternative methodology for controlling for confounding. | None |

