**6.1 Cohort Summary**

All patients with COPD, defined by 3 outpatient claims or 1 inpatient claim in the prior 3 years (PPV 0.82 [0.72-0.89]),^2^ who initiated a prescription for fluticasone-salmeterol (Advair HFA) (exposure) vs. fluticasone-salmeterol (Advair Diskus) (referent) between January 1, 2007 and November 30, 2023. We will require a 180-day washout period for both the exposure and the referent. We will also require 180 days of continuous insurance coverage prior to cohort entry. We will include patients who received other therapy in the baseline period (whether single-agent inhalers [ICS, LAMA, LABA], LAMA-LABAs, or triple therapy). In other words, we will include patients who may be stepping up therapy (from monotherapy), stepping down therapy (triple therapy), or switching (from LAMA-LABA). Following other studies, we will exclude patients who are less than age 40 to increase the specificity of COPD diagnoses. This will help further ensure that patients entering the cohort are receiving triple therapy for COPD rather than another respiratory condition.

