***Study period:***

Baseline Period: The baseline period is defined as 180 days prior and up to and including the cohort entry date [-180, 0] unless otherwise noted in the design diagram.

Follow up Period: The follow-up period starts 1 day after the cohort entry date and continues until censoring. For further details on censoring, see section 8.2.

***Note:*** All diagnosis, procedure and generic names of drugs are given in the file named “Protocol Appendix.”

| Steps |  |
| --- | --- |
| **6.2.1** | **Patients with prescription for Advair HFA/Diskus**  *Advair HFA is the exposure and Advair Diskus is the reference* **(fills of both on cohort entry are not allowed)**  **Date of prescription is called the index date**  [assessed between January 1, 2007 and November 30,2023]  *Appendix Table 1 “Exposure definitions,” variables names: Advair HFA, Advair Diskus* |
| **6.2.2** | **Exclude patients who do not have continuous insurance enrollment during baseline period**  [assessed between 180 days prior up to and including index date (-180, 0)] |
| **6.2.3** | **Exclude patients with no prior diagnosis of COPD**  [assessed 3 years prior to and including the index date (-1095, 0)]  *Appendix Table 2 “Exclusion criteria,” variable name: Diagnosis of COPD* |
| **6.2.4** | **Exclude patients who are under the age of 40**  [assessed on the index date (0, 0)] |
| **6.2.5** | **Exclude patients who received another ICS-LABA script (besides Advair HFA or Advair Diskus)**  [assessed between 180 days prior up to and including index date (-180, 0)  *Appendix Table 2 “Exclusion criteria,” variable name: ICS-LABA besides Advair* |
| **6.2.6** | **Exclude patients who started a LAMA, LAMA-LABA, or ICS-LAMA-LABA on the cohort entry date**  [assessed on the cohort entry date (0,0)] |

1. **Covariates**

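### The censoring rule for both primary outcomes omits LAMA, so follow-up after a LAMA is added to Advair still counts as index-device time

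*Protocol*

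**What the plan says.** The protocol's follow-up and censoring section (8.2) gives seven events that end follow-up for the primary effectiveness and safety outcomes. Three concern treatment:

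- Item (1): "discontinuation of index therapy (with a 60-day grace period between fills and a 60-day exposure risk window".
- Item (2): a switch between the two Advair devices.
- Item (3): "initiation of a different inhaler regimen (ICS, LABA, ICS-LABA, LAMA-LABA, ICS-LABA-LABA".

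The other four are death, end of coverage, end of data and day 365.

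Elsewhere the inhaler classes are named differently. Section 6.1 admits patients whose baseline therapy was "single-agent inhalers [ICS, LAMA, LABA], LAMA-LABAs, or triple therapy". Table 1 has separate rows for LAMA and for ICS-LAMA-LABA. Section 6.2.6 reads "Exclude patients who started a LAMA, LAMA-LABA, or ICS-LAMA-LABA on the cohort entry date". The entry ICS-LABA-LABA occurs only in item (3).

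**The concern.** Item (3) fixes which person-time is at risk in both primary analyses. It names LABA twice in its last entry and leaves LAMA out altogether. The reader cannot tell whether a LAMA started during follow-up ends it: the opening words of the item suggest that it does, and the list suggests that it does not. Two programmers could build different primary analysis sets from this text.

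At stake is what the hazard ratio measures. If LAMA starts are not censored, part of each arm's time is spent on Advair plus a LAMA, and outcomes in that time are credited to the device. This distorts the device comparison if such add-ons are more frequent, or come earlier, with one device than with the other.

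**Working it through.** **Step 1: set the class lists side by side.**

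| Class | Recognised at baseline (6.1, Table 1) | Start on day 0 excludes (6.2.6) | Start in follow-up censors (item 3) |
|---|---|---|---|
| ICS | yes | no | yes |
| LABA | yes | no | yes |
| LAMA | yes | yes | **no** |
| LAMA-LABA | yes | yes | yes |
| ICS-LAMA-LABA | yes | yes | **not as printed** |

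Other ICS-LABA products are excluded at baseline by 6.2.5 and are on the list in item (3). Of the three classes in 6.2.6, only LAMA-LABA also appears in item (3) as printed.

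**Step 2: follow four patients through items (1) to (7).**

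- *Adds a separate LAMA and keeps filling Advair.* Item (1) does not apply because fills continue. Item (2) does not apply because there is no device switch. Item (3) does not list LAMA. Items (4) to (7) have nothing to do with the step-up. The patient stays in follow-up, up to day 365.
- *Adds a separate ICS or LABA.* Censored by item (3), although both components are already in Advair.
- *Adds a LAMA-LABA.* Censored by item (3).
- *Replaces Advair with a single triple inhaler.* Read as ICS-LAMA-LABA, the last entry censors at the start. Read literally, it does not, and item (1) ends follow-up only after its 60-day allowances have run out.

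The gap that remains on any sensible reading is the first patient.

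**Step 3: is it handled elsewhere in the analysis?** The weights are built from Table 1 covariates assessed up to and including day 0. The Cox model has treatment as its only predictor. Baseline LAMA use is therefore balanced, but a LAMA started later is not. Among the sensitivity analyses, the grace-period analysis changes item (1). The one-year ITT analysis does not depend on item (3). None varies item (3) itself.

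**Step 4: size.** The protocol gives no rate of LAMA initiation by arm, so the bias cannot be computed. For scale only, assume that an added LAMA multiplies the exacerbation hazard by 0.8 and covers a share q of an arm's at-risk time. The HR (HFA vs Diskus) is then multiplied by

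(1 − 0.2 × q_HFA) / (1 − 0.2 × q_Diskus).

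- q equal in both arms: factor 1.
- 5% vs 15%: 0.99 / 0.97 = 1.02. Arms reversed: 0.97 / 0.99 = 0.98.
- 10% vs 30%: 0.98 / 0.94 = 1.04. Arms reversed: 0.94 / 0.98 = 0.96.

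The 0.8 and every q are assumptions. If patients who step up are sicker, the shift can run the other way. No such illustration is offered for pneumonia, because the protocol gives no basis for one.

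**The case against.** The strongest case against has four parts.

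*The omission may be deliberate.* The protocol never says that starting a LAMA should censor. A patient who adds one is still using the index device, and Advair with a LAMA is not foreign to a cohort that admits prior LAMA and triple-therapy users. This stands as a possibility. But no reason is given, and it fits poorly with censoring at a separate ICS or LABA.

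*Section 6.2.6 has another purpose.* A reader might infer that item (3) contradicts 6.2.6. The documents do not support that: 6.2.6 is an eligibility rule about simultaneous starts, it gives no reason, and the two lists need not match. It shows only that the protocol treats LAMA as a regimen in its own right.

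*The triple-therapy entry is a typing slip.* A reader might also infer that no step-up to triple therapy is censored. That is too broad. The opening words of item (3) cover a single triple inhaler, a LAMA-LABA add-on is listed, and item (1) eventually catches anyone who stops Advair.

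*The effect may be small.* The effectiveness outcome is time to first exacerbation, so a LAMA added after that event falls outside its at-risk time. The ITT analysis avoids the rule, and reasons for censoring will be reported by exposure. All of this is correct and limits the severity. However, ITT answers a different question, and the reported reasons for censoring depend on the same list.

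**Conclusion.** The point holds as a gap in the definition of at-risk time for both primary outcomes. LAMA is missing from the censoring list, so as written a separate LAMA added to continuing Advair does not end follow-up. The ICS-LABA-LABA entry is a slip to correct, not a second substantive defect.

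Bias arises only if LAMA step-up differs by device. Its size and direction are unknown, and the factors of 0.96 to 1.04 above rest wholly on assumed inputs; they should not be read as an estimate. That the authors meant LAMA to censor is a reasonable inference, not something the protocol states. Severity: moderate, because the rule governs both primary analyses and can be coded two ways, but a large bias has not been shown.

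**What to change.** In item (3), change ICS-LABA-LABA to ICS-LAMA-LABA and add LAMA to the analytic censoring list. Define initiation as a first fill of a class with no fill of that class in the 180-day baseline, so that patients admitted under 6.1 on an existing LAMA or triple therapy are not censored for continuing it.

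If leaving LAMA uncensored is deliberate, say so, give the reason, and add a sensitivity analysis that censors at LAMA initiation.

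Leave the list in 6.2.6 as it is. Using one common list would add ICS and LABA starts to the day-0 exclusion and change eligibility without argument.

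The cost is one line of text and one measure definition. Follow-up becomes slightly shorter. Censoring may also become more informative, since stepping up can be prognostic; the planned one-year ITT analysis is a check on that.

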The baseline covariate assessment period for all measures will start 180 days before cohort entry and will stretch up to and include the day of cohort entry with the following exceptions: (1) We will assess age, sex, race, region, year of cohort entry, and index prescription by a pulmonologist only on the day of cohort entry; (2) We will assess the presence of any prior asthma diagnosis using all available data and stretching up to (and including) the day of cohort entry. Diagnosis based covariates will be defined using any care setting and any diagnosis position unless otherwise specified. All codes for these variables are provided in Appendix Table 3, “Covariates.” The variable names are as listed below in Table 1. All variables listed below will be included in our propensity score model. We will use a missing indicator in our propensity score model in the case that data are missing for any covariates.

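### Both primary hazard ratios censor at treatment change but weight only for baseline covariates, so they can be biased in either direction, and no planned analysis corrects the on-treatment estimate

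*Protocol*

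**What the plan says.** Under Follow up and censoring, the list for the primary effectiveness and safety outcomes ends follow-up at, among other things:

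- item (1): "discontinuation of index therapy (with a 60-day grace period between fills and a 60-day exposure risk window";
- item (2): "switch from exposure to referent or vice-versa", with no lag stated;
- item (3): "initiation of a different inhaler regimen (ICS, LABA, ICS-LABA, LAMA-LABA, ICS-LABA-LABA", also with no lag stated.

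Death, disenrolment, end of data and 365 days complete the list.

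The Statistical analysis section builds the weights from a logistic CBPS model "including the variables in Table 1 as predictors of exposure". The Covariates section says the assessment window "will start 180 days before cohort entry and will stretch up to and include the day of cohort entry". Its exceptions are measured on the entry day or further back, never later. The hazard ratio then comes from a Cox model "with the treatment as the sole predictor and incorporating balancing weights from CBPS-IPTW". It is presented as an average treatment effect, without saying that it is an on-treatment effect.

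The plan is aware of the problem. Row 2 of the Sensitivity analyses table is a one-year ITT analysis whose stated strength is "This analysis will allow us to avoid informative censoring". Its stated weakness is that much of the person-time will be unexposed. Row 1 varies the grace period to 30 and 90 days. The Statistical analysis section promises follow-up duration and censoring reasons by exposure group. Row 4 of the sensitivity table says "Follow-up time will be low because patients discontinue their inhalers so frequently".

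**The concern.** A Cox model treats a censored patient as represented by those of the same arm who remain at risk. Weights fixed at entry make the arms comparable on day 0. They do not keep the patients who remain representative once people leave because their disease is getting worse.

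Stopping, switching device or changing regimen may well follow worsening symptoms. The Background notes more handling errors with metered-dose inhalers, which gives a plausible route by which treatment change could differ between arms. In the pneumonia analysis an exacerbation does not end follow-up, so a regimen change after an exacerbation could remove person-time at higher risk.

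At stake is whether a modest difference between devices, or its absence, on either primary outcome can be read as a device effect. If the on-treatment analysis shows a difference and ITT is near null, the planned analyses cannot separate bias in the first from dilution in the second.

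**Working it through.** The protocol gives no discontinuation rate, event count or target hazard ratio, so there is no figure to reproduce. The check has two parts.

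**1. Does any listed analysis correct the on-treatment hazard ratio?**

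- Row 1 (grace period 30 or 90 days) moves the censoring date but does not model censoring.
- Row 2 (ITT) removes treatment-change censoring by changing the contrast.
- Row 4 (drop the first 30 or 60 days) removes early follow-up.
- Rows 5 to 7 change outcome definitions.
- Rows 8 to 10 change baseline adjustment.
- The table of censoring reasons is descriptive.

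None corrects it.

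**2. When does bias arise, and how large can it be?** All inputs below are assumptions. Arms are exchangeable at baseline, which mimics perfect baseline weighting.

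*Weekly simulation, no lag.* 400,000 patients per arm and 52 weeks. The event hazard is 1% per week, tripled while a patient is in a worsened state. About 48% to 79% stop within the year. Stopping probabilities are per week.

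| Stopping pattern | As-treated HR, true HR 1.00 | As-treated HR, true HR about 0.90 |
|---|---|---|
| A. HFA 0.04, Diskus 0.02, unrelated to worsening | 1.001 | 0.901 |
| B. 0.02, rising to 0.08 when worsened, same in both arms | 1.005 | 0.904 |
| B2. Worsening triples stopping in both arms; HFA rate is double | 0.961 | 0.867 |
| C. HFA 0.02, rising to 0.06; Diskus flat 0.03 | 0.950 | 0.847 |
| C2. HFA 0.02, rising to 0.12; Diskus flat 0.03 | 0.890 | 0.800 |
| D. HFA 0.04, falling to 0.01; Diskus 0.02, rising to 0.06 | 1.095 | 0.995 |

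A and B show essentially no bias. B2 shows that the dependence on worsening need not differ by arm if the overall stopping rate does. Under the null the range is 0.890 − 1 = −11% to 1.095 − 1 = +9.5%. Stabilised censoring weights returned 0.998 to 1.003 (true 1.00) and 0.895 to 0.905 (true about 0.90). That is a best case, because the stopping probabilities were known and the worsened state was measured.

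*Daily simulation, with and without a 60-day lag.* True HR 1.00, 300,000 per arm, 365 days. The stop hazard is 0.004 per day. The event hazard is 0.001 per day, multiplied by 4 when worsened. Patients enter the worsened state at 0.003 per day and, if it is transient, recover at 0.02 per day. Worsening multiplies stopping in HFA by 3 or 5 and in Diskus by 1. The simulation standard error of the log HR is about 0.005.

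| Setting | No lag | 60-day lag |
|---|---|---|
| 3 vs 1, transient | 0.96 | 1.00 |
| 5 vs 1, transient | 0.94 | 0.99 |
| 5 vs 1, persistent | about 0.80 | 0.90 to 0.91 |

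A lag that keeps post-stop events removes most of the bias when worsening is transient and about half when it persists. Adding unlagged switching to the 5 vs 1 case brings bias back. The HR is 0.97 with transient worsening. With persistent worsening it is 0.87 to 0.91, depending on how much switching is assumed (0.87 when a quarter of the stop hazard is unlagged).

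**The case against.** The strongest reply is that an on-treatment primary analysis paired with an ITT sensitivity analysis is a coherent design. The plan names the threat, tests the grace period and will show censoring reasons by arm. The 60-day grace period and risk window for discontinuation absorb some post-stop events. Censoring weights need measured severity after entry, and claims lack symptoms and lung function; the Subgroup analyses table itself concedes that spirometry values are unknown. All of this stands. It limits the size of the concern and the power of the remedy, but still leaves the on-treatment estimate without a correction.

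A reader might also infer more than the documents support:

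- **That differing stopping by device by itself biases the hazard ratio.** Scenario A shows that it does not.
- **That the bias favours one device.** The documents give no data on direction, and handling errors are not the same as symptom-driven stopping. Scenarios C2 and D go opposite ways.
- **That treatment change is the commonest reason follow-up ends, or that most ITT person-time is unexposed.** The protocol says only that discontinuation is frequent and that much of the time is unexposed.
- **That the same censoring governs the recurrent-event analyses.** The list is headed for the primary outcomes only.
- **That every step-up censors.** Item (3) omits LAMA alone and prints ICS-LABA-LABA, so its scope is unclear.

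**Conclusion.** The concern holds in a conditional form. Both primary hazard ratios are exposed to dependent censoring that baseline weights cannot address. Bias arises if treatment change follows post-entry worsening and either its rate or that dependence differs by device. The direction is unknown.

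The size is also unknown. The null values of about 0.89 to 1.10 are illustrations from the no-lag weekly scenarios, not bounds. More persistent worsening gave about 0.80 without a lag and about 0.90 with one, and transient worsening with a 60-day lag gave values near 1.00. The concern is therefore weaker for discontinuation and sharper for items (2) and (3). The protocol fixes the primary model and itemises its sensitivity analyses, so this is a choice already made. It is a weakness to remedy before analysis, not an error that invalidates the design.

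**What to change.** 1. State that the primary estimand is an on-treatment effect over up to 365 days, in place of an unqualified average treatment effect.
2. Add a sensitivity analysis for both primary outcomes that multiplies the CBPS-IPTW weights by stabilised inverse probability of censoring weights for items (1) to (3). Estimate these separately by arm from the Table 1 covariates plus time-updated SABA fills, exacerbations, antibiotic fills, and ED and pulmonologist visits. Truncate at the 1st and 99th percentiles. Post-entry exacerbations inform the pneumonia model; in the effectiveness model the first one is the event itself.
3. Say whether a lag applies to items (2) and (3), reconcile the regimen list in item (3), and define the date on which each censoring weight acts given the 60-day window.
4. Report this estimate beside the primary and ITT results, and keep the grace-period analyses and the table of censoring reasons.

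The cost is extra programming on claims already held and somewhat wider intervals. The correction reaches only worsening that leaves a trace in claims, so agreement with the primary result would reassure without proving that bias is absent.
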